**Fig. 3 Fig3:**
[figure not shown]
Eight-channel electromyograph (EMG System do Brasil) equipment

Surface electromyography (sEMG) of right and left masseter (RM and LM) and right and left anterior temporalis (RT and LT) muscles will be acquired prior to application of the mandibular advancement oral appliance (OA_m_), the mastication apparatus (MA), and neuromuscular electrical stimulation (NMES), as well as 2 months after all therapies. During the sessions, the patient will be instructed to remain seated on a chair, feet apart, shoulders relaxed, and hands resting on their thighs, with their head turned to the Frankfourt parallel to the ground and no visual feedback of the signals displayed on the computer, in a well-illuminated, silent recording room in a comfortable position, with both eyes open. A short training period will be conducted prior to beginning the tests to familiarize the patient with the tasks. The skin of the patient will then be cleaned with a cotton ball soaked in 70% alcohol to reduce impedance. Next, pregelled, self-adhesive, bipolar, disposable 10-mm-diameter Ag/AgCl surface electrodes (MediTrace®) will be fastened over the right masseter (RM), left masseter (LM), right temporalis (RT), and left temporalis (LT) muscles, with an interelectrode distance of 10 mm, on the muscle motor point, after the patient has performed moderate intercuspation. Surface electrodes will be bilaterally fastened according to anatomical references and guided by the direction of muscle fibers at two points: the anterior temporal muscle, 2–3 cm superior–posterior distance to the lateral corner of the eyes in the region of greatest evidence of muscle mass, parallel to the muscle fibers, but with its sensing surface perpendicularly oriented; and the superficial portion of the masseter, 1–2 cm above the gonial angle of the mandible, in the region of greatest evidence of muscle mass, with muscle fibers parallel to the surface (Fig. 4). Also, a grounding electrode (Ag/AgCl 10-mm-diameter surface electrode; MediTrace®) will be fastened to the left wrist of the patients.

**Fig. 4 Fig4:**
[figure not shown]
Electrode placement for surface electromyography examination

#### Analysis of surface electromyography data

In order to obtain a frequency domain analysis, surface EMG signal processing will be carried out using specific routines conducted with the Matlab program, version 7.1 (The MathWorks Inc., Natick, MA, USA). In addition, the time domain analysis will be executed using the root mean square (RMS) of the EMG signal (expressed in μV) and will be normalized by the highest values of RMS obtained during the three MHI and MVC readings (μVmV/μV/100: % MVC). The data captured at rest (total of 15 s) will be used for both analyses during MHI and MVC (total of 3 s; the first and fifth seconds having been discarded).

#### Protocols for surface electromyography, mandibular force, and mouth opening

The selected protocol for sEMG is based on previous work [13, 15, 36]. The sEMG records will be acquired under the following conditions: rest (three sequential readings of 10 s each); maximum voluntary contraction (MVC) with cotton balls placed between the upper and lower molars on each side (three readings of 5 s each, with a 2-min interval between the readings); and voluntary contraction with maximum habitual intercuspation (MHI) with no material placed between the teeth (three readings of 5 s each, with a 2-min interval between the readings). After a 3-min interval, a mandibular force transducer (EMG System do Brazil) (Fig. 5) will be used to record the maximum bite force. This consists of a mechanical device with sensors that record material deformations during the bite. These deformations are converted into kilograms-force or Newtons by means of EMG Lab V1.1 software (EMG System do Brazil). The maximal opening amplitude will be measured with a specific caliper (Fig. 6).

**Fig. 5 Fig5:**
[figure not shown]
Mandibular force transducer (EMG System do Brazil)

**Fig. 6 Fig6:**
[figure not shown]
Caliper to measure mouth opening

#### Phases of the surface electromyography examination

The sEMG, referring to the bilateral masseter (surface portion) and to the temporal (anterior portion) muscles in rest, MVC, MHI, and bite force, shall be carried out in two distinct phases: Phase 1, initial data acquisition, prior to proposed therapies (Groups 1–3); and phase 2, treated groups (Groups 1–3) after 2 months of neuromuscular electrical stimulation, mastication apparatus with mastication instrument Hiperboloide®, and mandibular advancement oral appliance therapies. The obtained data will be compared among each group and among each person with themselves, to verify the effectiveness of the proposed therapies on the improvement of the masticatory muscle electrical activity, on the physiological sleep variables, and on salivary parameters in patients with DS.

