**Methods:**

The patients with DS will be randomly selected and divided into three groups (DS-NMES, DS-MA, and DS-OA_m_) with a minimum of 10 patients in each group. A thermosensitive microchip will be embedded in the OA_m_ to record its compliance. The therapeutic effects on masticatory muscle function will be investigated through electromyography, a caliper, and a force-transducer device; the sleep variables, in turn, will be evaluated by means of polysomnography. The physicochemical and microbiological properties of the saliva will also be analyzed, including the salivary flow, viscosity, buffer capacity, cortisol levels (susceptibility to psychological and/or physical stress), and *Pseudomonas aeruginosa* levels (risk of aspiration pneumonia) in these patients. The methods determined for this study will be carried out prior to and after 2 months of the recommended therapies.

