## Methods/design

This is a randomized, controlled, three-arm clinical trial conducted according to the ethical standards established in the 1961 Declaration of Helsinki (as revised in Hong Kong in 1989 and in Edinburgh, UK in 2000). This study was registered in the World Health Organization Universal Trial (UTN; number U1111-1201-3155) and Registro Brasileiro de Ensaios Clínicos (ReBEC; number RBR-3qp5np). It was also approved by the Brazilian Human Research Ethics Committee of the Institute of Science and Technology (CEPh 2.127.141; process number CAAE 64173616.4.0000.0077). All caregivers will be informed about the proposal therapies and will provide written informed consent. The whole study design (Fig. 1) and the SPIRIT checklist(aditional file 1) were followed. In addition, a SPIRIT figure is provided to illustrate the study schedule for the enrolment, interventions, and assessment (Fig. 2).

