### Subjects

Adult patients with Down syndrome (DS), aged between 18 and 40 years, will be recruited from institutions for people with disabilities. The survey will be conducted at the Center for Bioscience Applied to Patients with Special Health Care Needs (CEBAPE), Institute of Science and Technology—UNESP/SJC, Brazil. The study will include adult patients with DS, from both genders, presenting subjective sleep disorder symptoms, snoring, and/or apnea/hypoapnea index (AHI) > 5.0/h, satisfactory dental health, and preserved cognitive function which allows them to understand and to respond to verbal commands necessary to perform this research project, and who agree to participate by free will including an Awareness Term signed by the patient or by the people responsible for the patient. The researchers will obtain informed consent from assistants, patients, and/or caregivers prior to the study. Cognitive analysis will be carried out under simple commands, such as “open your mouth”, “close your mouth”, “bite”, and “relax”. If patients are able to answer these simple commands, then they will be considered as part of the study. The exclusion criteria include body mass index > 30, use of psychiatric medication, inability to reach the university when needed, signs of psychiatric disease, and having been exposed to physiotherapy and/or orthodontic treatment at least 6 months prior to the beginning of this study.

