### Statistical analysis

Whenever applicable, the data will be presented as average ± standard deviation. The paired *t* test will be used in order to compare continuous variables with normal distribution, prior to and after polysomnography, as well as specific therapies. If the data show a non-normal distribution, then the Wilcoxon test will be used. The groups will be compared to one another using ANOVA or Mann–Whitney U test, according to the distribution. *P* ≤ 0.05 will be considered statistically significant. Missing data will be treated as worst-case scenario imputation. All analyses will be performed using SPSS 16.0.

All data will be stored on a notebook exclusively for this purpose, as well as on a hard disk for increased safety of data storage. Data will be allocated to a file with a number that corresponds to each participant and will be managed by the assistants, not available to the professionals who will carry out the interventions.

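### Before/after tests within each arm share the role of verifying effectiveness with the between-arm tests, although no arm is untreated; only relative effects are protected by randomisation

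*Protocol article*

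**What the plan says.** Methods/design describes the study thus: "This is a randomized, controlled, three-arm clinical trial". The abstract's Methods paragraph has patients "divided into three groups (DS-NMES, DS-MA, and DS-OA_m_) with a minimum of 10 patients in each group", and each of these groups gets a therapy. Under Phases of the surface electromyography examination, the second measurement is "phase 2, treated groups (Groups 1–3) after 2 months of neuromuscular electrical stimulation" or one of the other two therapies. No untreated, sham or delayed-treatment group is described.

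That section also states how the data will be used: they are to be "compared among each group and among each person with themselves, to verify the effectiveness of the proposed therapies" on muscle activity, sleep and saliva. The Statistical analysis section carries this out in two ways. First, a t test on paired data, which "will be used in order to compare continuous variables with normal distribution, prior to and after polysomnography, as well as specific therapies", with this alternative: "If the data show a non-normal distribution, then the Wilcoxon test will be used". Second, the groups are compared with one another by ANOVA or the Mann–Whitney U test. Both are judged at 0.05.

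The Subjects section admits patients "presenting subjective sleep disorder symptoms, snoring, and/or apnea/hypoapnea index (AHI) > 5.0/h". Sleep is then recorded once before therapy and once after 2 months. The Discussion expects sleep quality to improve after all three therapies, which is a statement about each therapy rather than about differences between them.

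**The concern.** Randomisation makes the arms comparable with each other. It does not make an arm at 2 months comparable with the same arm at baseline. With three active arms, the only planned test that can appear to show that a therapy works at all is the paired one, and the plan gives that test an inferential role.

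If all three arms improve, as the Discussion expects, the between-arm tests may show nothing, and the paired tests would be the natural basis for an effectiveness claim. That claim could arise with three ineffective therapies. A second risk is that one arm with a significant paired test and another without could be read as a difference between them, which only the between-arm test can show.

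**Working it through.** The plan gives no figure for this bias, so there is none to reproduce. The check has four steps.

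**1. What each test estimates.** Let τ_k be the effect of therapy k relative to no treatment, and b the change that would occur without any therapy (time, attention, repeat testing, regression to the mean). Randomisation makes b the same in expectation in every arm.

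- Paired test in arm k: mean change = τ_k + b.
- Between-arm contrast: (τ_j + b) − (τ_k + b) = τ_j − τ_k.

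The paired test is valid for τ_k only if b = 0. The contrast is free of b but is zero when the therapies work equally well or equally badly. Neither gives τ_k.

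**2. Which parts of b apply to which outcome.** Patients are selected on sleep symptoms, snoring and/or AHI, so regression to the mean concerns sleep measures. They are not selected on EMG, bite force or saliva. Repeat-test effects concern effort-dependent tasks. The short training before the EMG tests reduces these but does not exclude them. Time and attention apply throughout.

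**3. Illustration for AHI only.** Assumptions, none of them in the document: standardised normal scores, test-retest correlation r = 0.7, no treatment effect. Baseline x is drawn above an entry cut c, and follow-up is y = r·x + √(1 − r²)·e with e standard normal. The expected shift is −(1 − r)·φ(c)/(1 − Φ(c)).

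- Cut at the population mean: −0.3 × 0.399/0.5 = −0.24 SD.
- Cut set so that 66% exceed it (the childhood prevalence of sleep apnea given in the Background, borrowed as an assumption): −0.3 × 0.366/0.66 = −0.17 SD.
- If half the patients enter on symptoms without AHI selection, these shifts halve to −0.12 and −0.08 SD.

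Simulated share of arms in which a two-sided paired t test at 0.05 declares improvement (nominal 2.5%):

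| Entry assumption | n=10 | n=15 |
|---|---|---|
| All selected, cut at the mean | about 15% | about 21% |
| All selected, 66% exceed the cut | about 9% | about 12% |
| Half selected, cut at the mean | 6–7% | about 8% |
| Half selected, 66% exceed the cut | about 5% | about 6% |

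In simulations with every patient selected, a between-arm ANOVA on change kept its 5% error rate.

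**4. Consequence for the sample size.** The Sample size section states 10 per group for 90% power at two-sided 0.05, plus 5 for dropout. The arithmetic agrees: 10 + 5 = 15 and 3 × 15 = 45. The 10 itself cannot be reproduced, because neither an effect size nor the contrast is stated. Back-solving 90% power at n=10 gives:

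- a paired standardised change of 1.15, or
- a two-arm difference of 1.53 SD, or
- a three-arm ANOVA effect f of 0.69.

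If 1.15 was a paired effect and is used as a between-arm standardised difference, power is about 68% at n=10 and 86% at n=15, before any baseline adjustment.

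**The case against.** The strongest reply is that the randomised comparison is already planned. This is correct: the sentence on verifying effectiveness names comparison among the groups as well as within persons, and the Statistical analysis section specifies the between-group tests. A reader might infer that effectiveness rests on within-arm tests alone; the document does not say so. What stands is that the paired tests are given the same purpose, and that the between-arm tests cannot speak to improvement over no treatment.

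Other objections also have force:

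- **Entry AHI.** A reader might take it to be a single-night value that is then reused as baseline. The Subjects section gives no source for it, and its and/or wording lets patients enter with no AHI selection. The illustration is therefore sensitive to the entry assumption, as the table shows.
- **Reach of the figures.** Combining three arms at 15% to 21% each gives 1 − 0.85³ = 39% to 1 − 0.79³ = 51% of trials with at least one false improvement. It is tempting to read this as the trial's error rate. It holds only for AHI with every patient selected, and not for EMG, bite force or saliva.
- **Safeguards.** EMG training, normalisation of the EMG signal to maximal readings, and blinded evaluators all help. None removes change over time or regression to the mean, and no such normalisation is described for bite force.
- **The word controlled.** An active-comparator trial is controlled, so the label is not an error.

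**Conclusion.** The point holds in this limited form. Two analyses are assigned to verifying effectiveness. One supports only relative effects; the other is uncontrolled, and randomisation does not protect it. This follows from the stated arms, tests and purpose, and rests on no assumption about size.

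The size cannot be derived from the document. For AHI alone, under the assumptions of the illustration, the rate of false improvement per arm runs from about 5% to about 21%, against 2.5% nominal, and depends mainly on how many patients enter through AHI. For muscle and salivary outcomes no figure can be given. The trial can still support claims about how the three therapies compare.

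**What to change.** In Phases of the surface electromyography examination and in Statistical analysis:

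- Name the randomised between-arm comparison at 2 months, adjusted for the baseline value already collected and reported with 95% CI, as the efficacy analysis.
- Label the paired t and Wilcoxon tests descriptive, and remove verification of effectiveness as the purpose of the within-person comparison.
- Reword the aims and the planned conclusions to the relative effects of NMES, MA and OAm, and state that improvement over no treatment cannot be concluded.

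In Sample size, say which contrast the 10 per group and 90% power refer to. If it was a paired contrast, restate the power for the between-arm comparison.

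Cost: no new data. The claim becomes more modest, and the restated power may be lower: about 68% at n=10 and 86% at n=15 in the paired case above, before the gain from baseline adjustment.

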#### Protocol for polysomnography

All patients will undergo the PSG type II home sleep test (Embla Embletta MPR + PG ST + Proxy; Natus, CA, USA) in their own house. The PSG will be performed prior to and after 2 months of all proposed therapies. During the night, a sleep technician will visit each patient’s home for examination preparation. All recording sensors will be placed according to recommended PSG techniques, using a gel-covered transducer, tapes, or elastic straps. The following biological signals will be recorded simultaneously and continuously: six channels for the electroencephalogram (EEG) (F4–M1, C4–M1, O2–M1, F3–M2, C3–M2, O1–M2), two channels for the electrooculogram (EOG) (E1–M2, E2–M2), four channels for the surface electromyogram (muscles of the submentonian region, anterior tibialis muscle), one channel for the electrocardiogram (derivation V1 modified), two channels for airflow (oronasal thermistor, nasal pressure transducer), two channels for respiratory effort (chest and abdomen, via x-trace belts), one channel for snoring, and one channel for body position, via EMBLA sensors. Arterial oxygen saturation (SaO_2_) and heart rate will be recorded via an EMBLA oximeter. All sleep staging and EEG arousals, respiratory events, and leg movements will be visually scored according to the *American Academy of Sleep Medicine (AASM) Manual for the Scoring of Sleep and Associated Events*, version 2.2, which is the definitive reference for standardized sleep monitoring and scoring [37]. The patients will be instructed to remain as relaxed as possible and to sleep naturally, as if at home. All signals will be recorded continuously. In the morning, an experienced polysomnography technician will remove the PSG equipment from the patient. A sleep physician will read and interpret all PSG examinations.

#### Protocol for salivary parameters

##### Saliva sample collection

Five steps will be defined in order to analyze the physical (determinations of the salivary flow and viscosity), chemical (buffer capacity and cortisol levels), and microbiological (levels of *P. aeruginosa*) properties of the saliva. In the first step, the patient must ingest no drink or foods for 2 h before saliva collection. The second step is rinsing the mouth thoroughly with distilled or deionized water (20 ml) for 20 s and collecting saliva samples 30–40 min after rinsing. The third step is to analyze the physical properties; a gustatory sialagogue will be applied as drops on the back of the tongue for 5 min, at an interval of 4 drops/min, to stimulate the saliva in patients with muscular hypotonicity and cognitive deficit. In order to analyze the chemical properties, the digital mechanical stimulation or milking of the major salivary glands will be carried out for 5–10 min. In the fourth step, simultaneously, the salivary flow will be aspirated by means of a low-power suction device (Aspiramax MA 520; NS, São Paulo, Brazil) and placed in a graduated sterile test tube which will be refrigerated at a temperature of 4 °C. In the fifth step, the saliva samples will be stored in a container at a temperature of 4 °C and later transported to the genome laboratory. In order to ensure identification of the *P. aeruginosa* species, the saliva sample must be analyzed within a maximum period of 3 h.

#### Analysis of the physical salivary properties of the saliva

##### Method for measurement of the saliva flow

After comfortable and postural adaptation of the patients on the chair, the saliva will be stimulated through a gustatory sialagogue, and then continuously collected for 5 min by means of a Falcon-type sterile tube which will be coupled to an aspirating pump. The saliva flow (SF) will be calculated by the formula: SF = total salivary volume / salivary collection time. The reference values are described in the study by Gomes et al. [38].

##### Method for measurement of the salivary viscosity

Saliva viscosity (texture) will be considered as this physical property strongly helps in regular swallowing. In light of this, the viscosity will be evaluated by means of an Ostwald viscometer, model Cannon-Fenske Routine, size 350, internal capillary with a caliper of 1.52 (Hermex Indústria e Comércio de Vidros para Laboratório, São Paulo, Brazil). Reference values (centipoise) are < 1.5 cp for nonviscous saliva and ≥ 1.5 cp for viscous saliva. In order to standardize the testing temperature, the viscometer will be vertically positioned by the “L” tube in a thermal bath at 37 °C for 15 min. A sample of 5 ml of saliva samples will then be inserted into the “N” tube of the Ostwald viscometer, using a hypodermic syringe. Concomitantly, aspiration will be carried out by inserting the pear into the “L” tube opening to force the saliva toward the “E” mark of the “C” bulb. Thereafter, the vacuum will be released and the saliva outflow time, between the “E” and “F” marks, will be clocked. This methodology is described in the studies by Almeida et al. [39] and Pedersen et al. [40].

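### The 37 °C step in the viscosity test conditions the viscometer before the saliva is in it, so the sample's temperature at timing is not standardised

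*Protocol article*

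**What the plan says.** All references are to the protocol article.

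The section on salivary viscosity states the purpose of the bath and what goes into it: "In order to standardize the testing temperature, the viscometer will be vertically positioned by the" first of the two tubes that it names. The conditions of the bath are given as "tube in a thermal bath at 37 °C for 15 min". Only after this does the sample, 5 ml in volume, enter the instrument: "saliva samples will then be inserted into the" second tube. Suction goes with filling: "Concomitantly, aspiration will be carried out by inserting the pear into the" first tube. The reading follows: "Thereafter, the vacuum will be released and the saliva outflow time, between the" two marks, is clocked. Saliva below 1.5 cp is classed as nonviscous, and 1.5 cp or more as viscous.

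The section on saliva sample collection names viscosity among the properties that its five steps serve. Step three concerns the physical properties and stimulation. In step four the saliva, aspirated at the same time, is "placed in a graduated sterile test tube which will be refrigerated at a temperature of 4 °C". Step five says that "the saliva samples will be stored in a container at a temperature of" again 4 °C, before transport to the laboratory.

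**The concern.** The viscosity of a liquid depends on the temperature of that liquid. A 15 min bath sets the testing temperature only if the sample is in the bath during those minutes. In the order given, the bath time has passed before the saliva enters, and filling, aspiration and timing follow with no stated wait. The temperature at which the outflow is clocked then depends on how warm the sample was on arrival and how quickly the operator works, and neither is fixed.

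The abstract lists viscosity among the salivary measures and makes the salivary physicochemical properties a secondary outcome. The statistical analysis section compares before with after within patients, and the groups with one another. Variation in reading temperature would add noise to those comparisons. A reading below 37 °C would also be too high against the 1.5 cp reference value if that value refers to saliva at 37 °C.

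**Working it through.** The document gives no calculation behind the 1.5 cp value, so there is no figure of the plan to reproduce. The check has two parts.

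**1. Order of steps (viscosity section)**

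| Order | Step | Is saliva in the bath? |
|---|---|---|
| 1 | Viscometer at 37 °C for 15 min | No |
| 2 | 5 ml of saliva inserted | From here, if the viscometer stays in the bath |
| 3 | Aspiration, concurrent with filling | Time not given |
| 4 | Outflow clocked | Time not given |

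No step pre-warms the saliva or holds the filled instrument.

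**2. Possible size**

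Inputs from the document: bath at 37 °C, storage at 4 °C, cut-off 1.5 cp.

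Assumptions not in the document:
- Saliva viscosity changes with temperature as that of water does: μ(T) = 0.02414 × 10^(247.8/(T + 273.15 − 140)) cp, with T in °C. This gives μ(4) = 1.547 and μ(37) = 0.690.
- The viscometer stays in the bath with its wall at 37 °C. The saliva is a cylinder of radius R = 3, 5 or 7 mm that warms by conduction, with diffusivity α = 1.45 × 10⁻⁷ m²/s.

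Mean sample temperature after t seconds, from a 4 °C start:

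T(t) = 37 − 33 × Σ (4/kₙ²) exp(−kₙ² α t/R²), where kₙ are the zeros of the Bessel function J₀.

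The leading time constant is R²/(5.783 α) = 11, 30 and 58 s for the three radii. The inflation factor is μ(T)/μ(37).

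Worked example, R = 7 mm, t = 60 s, leading term only: (4/5.783) × exp(−60/58.4) = 0.692 × 0.358 = 0.248. So T = 37 − 33 × 0.248 = 28.8 °C, and the factor is about 1.18.

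| Time from filling to clocking | R = 3 mm | R = 5 mm | R = 7 mm |
|---|---|---|---|
| 10 s | 1.21 | 1.45 | 1.61 |
| 30 s | 1.03 | 1.19 | 1.35 |
| 60 s | 1.00 | 1.06 | 1.18 |
| 120 s | 1.00 | 1.01 | 1.06 |
| 900 s (15 min) | 1.00 | 1.00 | 1.00 |

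Reading against the cut-off, in the slowest-warming column: at 30 s, saliva of 1.5/1.35 = 1.11 cp or more at 37 °C would read as viscous; at 60 s, saliva of 1.5/1.18 = 1.27 cp or more.

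If the sample starts at an assumed room temperature of 22 °C, the largest factors are 1.14 at 30 s and 1.08 at 60 s.

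Warming may also be slower than this model. With assumed first-order time constants of 30 to 180 s, a sample from 4 °C would be at about 9 to 25 °C after 30 s, 13 to 33 °C after 60 s and 31 to 37 °C after 300 s. The size therefore rests on details that the document does not give. That 15 min after filling is ample under the conduction model does not depend on which of the three radii is used.

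**The case against.** **The sample may not be cold.** Step three of the collection section speaks of analysing the physical properties before refrigeration and storage are mentioned. Step five ties storage to transport to the laboratory, and the flow section mentions no cooling. This stands in part: the 4 °C start is the more natural reading, because step four cools the saliva as it is aspirated, but it is not certain. Saliva at room temperature would still be below 37 °C.

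**The error may be small.** The viscometer is never said to leave the bath, so the saliva enters warm glass. A reader might infer that readings are inflated as they would be at storage temperature, by 1.547/0.690 = 2.24 times. The document does not support that as the expected size: it would need clocking with no warming at all.

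**Laboratory detail is often condensed in an article, and the section cites two method papers.** These may include a hold after filling, which cannot be checked here. But the article does not leave temperature control to another source. It states the control, its purpose, its duration and its place in the sequence, and that place does not serve the purpose.

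**The trial is little affected.** This largely stands. All arms use the same procedure, and the quality control section provides for blinded evaluators. A constant offset would largely carry through both visits. The statistical analysis section names no test for a classification at 1.5 cp, and the aims list salivary tests without naming viscosity. A reader might infer bias between groups, or a spurious change between visits; nothing in the document shows that handling differs by arm or by visit.

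**Conclusion.** The point holds in a limited form. As written, the step meant to standardise the testing temperature is completed before the saliva is in the viscometer, and no hold follows, so the temperature of the saliva at timing is not controlled.

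That conclusion rests on the order of steps alone. Its size rests on assumptions: water-like behaviour, a 4 °C start and conductive warming in the bath. These give about 1.0 to 1.35 times the 37 °C value at 30 s and 1.0 to 1.18 times at 60 s, more if clocked at once and less from a warmer start. Since the time from filling to clocking is not stated, the true size is unknown.

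The consequence is possible noise in the before-and-after comparison of a secondary outcome, and readings that can be pushed over the 1.5 cp reference value. The primary outcomes are not touched. The correction is worth making because it is simple, not because the trial's main conclusions depend on it.

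**What to change.** Reorder the viscosity procedure. Load the saliva first. Hold the filled viscometer, or the closed sample tube together with it, in the 37 °C bath for the 15 min already planned. Then aspirate to the mark and clock. Apply the same rule at baseline and at 2 months. It would also help to say whether the viscosity sample goes through the 4 °C steps.

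The cost is a change of wording; the bath and the 15 min are already in the plan. One small check is needed: confirm that the 1.5 cp reference value refers to saliva equilibrated at 37 °C. If it was obtained with the present order of steps, the reordered readings would not be strictly comparable with it.
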